### Study setting

This is a single centre study will be conducted at LSTM in the Accelerator Research Clinics. This bespoke facility is host to experimental human pneumococcal colonisation work in Liverpool with clinical and laboratory staff expert in delivery of controlled human infection model studies. The facility includes dedicated clinical areas; a pharmacy with access to a Qualified Person (QP); and category two and three microbiology and immunological laboratories.

### Controlled human infection model recruitment in the COVID-19 pandemic

During the COVID-19 pandemic, the LSTM group successfully enrolled more than 1000 participants to the ChAdOx1 nCoV-19 vaccine (Astra-Zeneca) phase III trial
^
19
^. During this period, we have established standard operating procedures to rigorously maintain participant, staff and community safety when attending the facilities. The study site is COVID-19 secure with systems in place to always ensure distancing and minimal access to communal areas. We have set strict inclusion and exclusion criteria to ensure that our participants are not at increased risk of severe COVID-19 disease, including that participants should have received at least two COVID-vaccines ≥ four weeks before study enrolment. In addition, our target age group of 18–50 has a relatively lower risk of severe COVID-19 disease compared to older populations. If COVID is detected (by rapid antigen testing prior to BCG challenge), participants will be temporarily suspended from the study, remaining under observation.

### Participant identification

**
Study participants
**

Eligibility assessment will be completed in stages:

•   Screening: study nurse or doctor checks that as part of the consent process the potential participant meets all the general screening criteria (
Table 2).

•   Eligibility is confirmed on the screening and follow-up visits. If any STOP criteria (see
Table 3) are met, the participant is excluded from and/or exits the study. Eligibility will be signed off by a medical doctor on the eCRF prior to primary intradermal injection.

### Inclusion criteria

•   Healthy adults aged 18–50 (inclusive)

•   Resident near LSTM (<1hr drive) for the duration of the study period

•   Allows the investigators to discuss the volunteer’s medical history with their GP

•   Females of childbearing potential with a negative urine pregnancy test at screening and willing to practice adequate birth control measures during the study.

•   Fluent spoken English - to ensure a comprehensive understanding of the research project and their proposed involvement

•   Capacity to provide written informed consent

•   Able and willing (in the investigators opinion) to comply with all the study requirements

### Exclusion criteria

Exclusion criteria will be self-reported and/or confirmed from GP questionnaire (GPQ) or medical summary if deemed necessary at research clinician discretion

•   Laboratory evidence at screening of latent M.
*tb* infection as indicated by a positive ELISPOT response to ESAT6 or CFP10 antigens
^
a
^

•   Clinical, radiological, or laboratory evidence of current active TB disease
^
b
^

•   Previous vaccination with BCG, or any candidate TB vaccine

•   Within the last year had close household contact with an individual with smear positive pulmonary tuberculosis

•   Clinically significant history of skin disorder, allergy, immunodeficiency (including HIV), cancer, cardiovascular disease, respiratory disease, gastrointestinal disease, liver disease, renal disease, endocrine disorder, neurological illness or psychiatric disorder.

•   Current medical issues

○Acute respiratory tract infection in the four weeks preceding recruitment○Any uncontrolled medical or surgical condition at the discretion of the study doctor

•   Maternal

○Female participants who are pregnant○Female participants who are lactating○Female participants who intend to become pregnant during the study○Female participants who are unable to take contraception measures during the study

•   Smoking

○Current (defined as ≥5/week) or ex-smoker (cigarettes / cigars / e-cigarette / vaping / smoking of recreational drugs) in the last 6 months.○Previous significant smoking history (more than 20 cigarettes per day for 20 years or the equivalent [>20 pack years]).

•   Current alcohol and recreational drug use

○Regularly drinks ≥3units/day (male) or ≥2units/day (female)○Uses recreational drugs○Participants may be excluded at the discretion of the research clinician

•   Concurrent oral or systemic steroid medication or the concurrent use of other immunosuppressive agents

•   History of anaphylaxis to vaccination or any allergy likely to be exacerbated by any component of the challenge agent

•   Has received any vaccination within one month of screening visit.

•   Has not completed at least two COVID-19 vaccination doses

•   Any abnormality of screening blood or urine tests that is deemed to be clinically significant or that may compromise the safety of the volunteer in the study
^
b
^

•   Positive HBsAg, HCV or HIV antibodies

•   Current involvement in another trial that involves regular blood tests or an investigational medicinal product
^
c
^

•   Use of an investigational medicinal product or non-registered drug, live vaccine, or investigational medical device for four weeks prior to dosing with the study challenge agent

•   Administration of immunoglobulins and/or any blood products within the three months preceding the planned challenge date

•   Participants who meet STOP criteria at the time of screening (see
Table 3)

•   Any other issue which, in the opinion of the study staff, may

○Put the participant or their contacts at risk because of participation in the study,○Adversely affect the interpretation of the study results, or○Impair the participant’s ability to participate in the study.

a: Participants discovered to have evidence of latent
*M. tb* infection as defined by a positive ELISPOT test will be referred for a plain chest x-ray. If there is any evidence of active TB disease either on clinical or radiological grounds, further investigation and treatment will be offered under the supervision of a consultant physician in respiratory medicine or infectious diseases.

b: Participants who are excluded from the study because they have been discovered to have a previously undiagnosed condition thought to require further medical attention will be referred appropriately to their GP or an NHS specialist service for further investigation and treatment.

c: Participants will be excluded from the study if they are concurrently involved in another trial that involves regular blood tests or an investigational medicinal product. To check this, participants will be asked to provide their National Insurance or Passport number (if they are a non-British citizen) and will be registered on a national database of participants in clinical trials (
www.tops.org.uk).

### Temporary exclusion criteria

The following are temporary exclusion criteria to inoculation:

Current infective illness and/or acute infective illness within 14 days of inoculation if COVID-19 negativePositive COVID-19 swab whether symptomatic or asymptomatic within 14 days of inoculationCurrently isolating following exposure to COVID-19Antibiotic use within 28 days of intradermal challenge

**Participants that have been temporarily excluded due to a positive COVID-19 swab, will require a negative lateral flow test prior to subsequent intradermal challenge**

Potential participants who are temporarily excluded at screening or prior to inoculation may be re-screened at a later date to assess inclusion into the study. There is no limit to re-screen a potential participant, however, participants would be re-consented if the time since initial written informed consent is greater than 4 months. Participants who meet any of the temporary exclusion criteria may have their participation delayed until resolution of the temporary exclusion criteria or, if this is not possible, will be not analysed as per protocol. If a participant unexpectedly requires a vaccination during the study period, they will remain in the study and will be considered as a part of an intention-to-treat subgroup for the purposes of analysis.

### Protocol procedures

**
Screening and eligibility assessment
**

Potential participants will be invited to participate in the study using ethically approved advertisements. The following recruitment methods may be utilised to identify and recruit potential participants:

•   Posters/leaflets/large outdoor banners in public and private areas, including but not limited to universities, libraries, golf clubs, community buildings, public buildings, and workplaces including bus and car adverts (all dependent on permission of managers/employers).

•   The intranet/internet/email lists of local universities, colleges, schools, workplaces

•   Social media including Facebook, Instagram, TikTok and Twitter.

•   Local press, television and radio, aiming to include articles/advertisements about the study/interviews with research staff/participants/research ambassadors (with consent).

•   Participants may be approached who are on our mailing list who have previously expressed interest in volunteering for previous studies and are happy to be contacted about future research.

•   Participants may be approached based on their prior consent to receive generic research communications (for example, Accelerator Research Clinic Volunteer Database, the Consent4Consent database or other database).

•   Open Exeter database: Potential study participants will be identified via National Health Applications and Infrastructure Services (NHAIS) who hold the central NHS patient database (Open Exeter). These databases will identify all persons within the local area who are in the appropriate age range. First contact to potential participants will not be made by the researchers. The initial information about the study will be sent out from this agency to preserve the confidentiality of potential participants. Potentially eligible participants will be sent an invitation, which briefly describes the study. Anyone who is interested in taking part will be able to contact the study team by telephone, text or email. Potential participants will then be sent the PIL.

•   We will advertise through community newsletters.

•   We will post flyers in nearby residential locations and do a flyer mail out in nearby residential locations (including mail drops).

•   We will approach people at public engagement events such as International Clinical Trials Day, World Pneumonia Day and other public engagement events3.

•   Sending invites to the public living in a geographical area from the electoral roll.

•   Social or community groups specific to age and target population.

•   We will ask pharmacies to distribute flyers to people collecting prescriptions or display recruitment materials.

•   University announcements pages, mailing lists their social media and freshers events

•   Large local employers to send the REC approved website text with weblinks and fliers out to their employees via email or through their newsletters.

•   We will approach people at asymptomatic swabbing centres and provide fliers or ask them to register on our Accelerator Research Clinic Volunteer Database

•   Other research teams.

The above is not an exhaustive list and further recruitment methods may be utilised if required. Several of the recruitment methods listed above may not be possible during the COVID-19 pandemic. During our recruitment efforts, we will ensure that we always follow government advice, UKHSA guidelines and COVID-19 secure practices

Interested persons are asked to contact the research team by phone or email for further information. Participants who are interested in research can also contact the study team using our established SMS text service. Potential participants will be sent a copy of the participant information leaflet (PIL) and invited to contact a member of the research team if they are still interested in participating. Provided we have not exceeded our capacity for recruitment, prospective participants will be given an unrestricted amount of time to decide whether to participate or not.

### Informed consent

Potential participants will be invited to discuss the study during a 60-minute appointment (including a 30-minute presentation) that may occur as a group discussion. In that circumstance we will follow the latest UKHSA guidance relating to COVID-19. We may use video communication to facilitate this as a group or individually. Participants will be able to discuss consent one-to-one with a registered healthcare professional (doctor or nurse), who is trained in consent, the trial protocol and GCP, and is delegated as per the delegation log. Individuals will be allowed to discuss the study and ask questions privately (if not answered in the group discussion). Potential participants will be asked how long they would like to consider the information and whether they need more time to come to a decision.

To assess capacity to provide consent, participants will be asked to demonstrate that they have understood by communicating their understanding of the study’s objectives, associated risks and potential benefits. This will include completion of a multiple-choice consent quiz to demonstrate their understanding of the study and to ensure researchers have communicated the study information appropriately. Any incorrect answers will be explained by the researcher, with an option to retake the quiz again.

If individuals agree to participate in the study, the study team are satisfied that they meet the eligibility criteria and the participant has voluntarily decided to take part in the research, they will be invited to provide written informed consent and further clinical appointments will be made. The consent form includes an option for participants to allow the DNA/RNA from these blood samples to be studied.

A specific written consent will be taken for skin punch biopsy at the initial consent stage. The consent will be reaffirmed on the day of the procedure, by the health professional performing the procedure.

The participant information leaflet (PIL) and presentation (presentation will be based on PIL) will inform them that they may withdraw from the study at any time and that this will not affect the care they receive within the NHS.

Any queries about possible eligibility will be discussed with the CI. A General Practitioner Questionnaire (GPQ) may be sent for specific information regarding medical history, medications and vaccinations if indicated following the medical history at consent. GP questionnaire/ summary will only be requested if indicated during the eligibility assessment and medical questions at consent. This will be reviewed by the study doctor prior to the vaccination appointment if applicable. A continuous verbal consent approach will be used throughout the study at each visit to confirm they are willing to continue.

As part of recommended practice (MRC tissue and biological samples for use in research) participants will be asked to consent to gift their samples for use in future studies and shared with collaborators internationally. All samples will be anonymised.

### The Over-volunteering Prevention System (TOPS)

Consent will be sought to register participants onto The Over-volunteering Prevention System (TOPS) database to guard against the potential for harm that can result from excessive volunteering in clinical trials. This will be done using the participants National Insurance number or passport number (if not a British citizen).

### Randomisation

Participants will not be randomised within this study.

### Blinding and code breaking

Participants and researchers will not be blinded within this study.

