## Protocol

### Objectives and outcome measures

**
Overarching aim
**

To establish the safety and feasibility of an established BCG controlled human infection model in Liverpool, UK.

**
Specific objectives (
Table 1)
**

1.   Confirm microbiological and molecular recovery of BCG at the intradermal injection site by gold standard skin punch biopsy (punch biopsy) 14 days after challenge

2.   Confirm safety and tolerability in healthy adult participants

3.   Determine agreement between less invasive skin biopsy techniques (including swabs, skin scrapes and microbiopsy) compared to gold standard punch biopsy on microbiological and molecular recovery of BCG with an aim to employ less invasive methods within a refined protocol in future.

4.   Confirm optimal procedures to assess immune response to BCG intradermal challenge locally (skin tissue), systemically (blood) and in the respiratory mucosa (nasal samples).

**Table 1. T1:** Outcome measures: Objectives and endpoints.

	Objectives	Endpoints
**Primary**	To quantify BCG recovered from the intradermal BCG challenge site 14 days after injection	Culture and PCR quantification of BCG at intradermal challenge site by punch biopsy
**Secondary**	Confirm safety and tolerability of study procedures in participants	Actively (solicited) and passively collected data on adverse events
	Confirm agreement between BCG recovery between punch biopsy and minimally invasive skin biopsy	Pairwise comparison between culture and PCR quantification by punch and micro skin biopsy
	Confirm agreement between BCG recovery between punch biopsy and minimally invasive skin scrape	Pairwise comparison between culture and PCR quantification by punch biopsy and skin scrape
	Longitudinal quantification of BCG recovery from the intradermal BCG challenge site at 2, 7, 14, 21 and 28 days	Culture and PCR quantification of BCG at intradermal challenge site by non-invasive skin swab.
	Confirm laboratory assays for immune response to BCG at intradermal injection site	Skin biopsy cell pellet(s) examined for immune cell differentiation and antigen stimulation
	Confirm laboratory assays for immune response to BCG in systemic circulation	Immune cell activation and functional assays; and cytokine levels in blood
	Measure immune response to BCG injection in respiratory mucosa	Nasal scrape pellet and nasal lining fluid examined for cell differentiation and activation and cytokine expression

**
Study hypotheses
**

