### Study design

Prospective longitudinal controlled human infection study after intradermal injection with BCG SSI in two phases: Phase A is designed to confirm microbiological recovery and determine agreement between the current gold standard of skin punch biopsy 14 days after injection with minimally invasive biopsy techniques. Phase B is designed to refine and optimise immunological assays to measure local (using optimal minimally invasive techniques), systemic (blood) and respiratory mucosal responses to intradermal BCG injection.

**
Phase A
**

Ten participants will receive a single intradermal injection to the upper arm of BCG SSI 6–24 × 10
^5^ colony forming units in line with an optimised and established existing protocol
^
15
^. The BCG SSI strain has been chosen as the UK licensed vaccine for TB. The dose (3x higher than that used in routine vaccination) has been chosen based on study findings by Minhinnick
*et al.*
^
15
^, who demonstrated good mycobacterial recovery at this concentration with no increase in participant adverse events between the doses. Participants will be followed up longitudinally with active assessment for tolerability; adverse events; and serious adverse events. We will determine BCG SSI recovery from the intradermal injection site 14 days later by classical microbiology and molecular diagnostic techniques using gold standard punch biopsy
^
15
^ as our primary outcome measure. In parallel, and after local anaesthetic injection, we will obtain paired minimally invasive samples (skin swab, skin scrape
^
18
^ and microbiopsy
^
17
^ from the same skin site at 14 days and determine agreement of BCG SSI recovery by classical microbiology and molecular diagnostic techniques with punch biopsy

Parameters for progression from Phase A to Phase B are:

1.Participants able to tolerate study procedures2.No experimental challenge related SAE or SUSAR detected3.Confirmation of BCG recovery by classical microbiology or molecular techniques from punch biopsy at day 14 in all 10 participants who received intradermal BCG challenge4.Confirmation of BCG recovery by classical microbiology or molecular techniques from any of the minimally invasive skin sample technique (swab, scrape and microbiopsy) at day 14 in ≥9 participants who received intradermal BCG challenge.

**
Phase B
**

Twenty participants will receive a single intradermal injection to the upper arm of BCG SSI 6–24 × 10

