https://www.nanopass.com/). After intradermal injection, participants will stay in the unit for 15 minutes and have a clinical review at this point. During the administration of the challenge agent, resuscitation medicines and equipment will be immediately available for the management of anaphylaxis.

**
Safety procedures
**

Written and verbal instructions are given to the participant describing potential mild, moderate and severe symptoms and the instances to consult the study team.

Participants will be instructed to monitor the development of any symptoms and report them to the clinical team immediately. Home monitoring of symptoms will include a clear flow chart of the necessary intervention should any symptoms develop (see participant safety information sheet).

**
Confirmation and quantification of mycobacterial recovery
**

Skin biopsy specimens will be cryopreserved and subsequently processed in batch. Typically, each biopsy specimen will be thawed in a 37°C water bath and transferred to an appropriate tissue homogenising platform
^
16
^. A total of 100 μL of neat homogenate and 100 μL of a 10
^-1^ dilution, in sterile PBS, will be plated in triplicate onto Middlebrook 7H11 agar. The BCG SSI vaccine vials will be reconstituted in PBS, and 100 μL of appropriate dilutions will be plated in triplicate as positive controls. Plates will incubated at 37°C for 4 weeks before counting. The remaining biopsy specimen homogenate will be stored at −80° for subsequent DNA extraction.

**
DNA extraction
**

Biopsy specimen homogenate will be thawed, and BCG DNA from 200 μL of homogenate will be released using standard methods. Typically, a tough microorganism (bead beating) lysing kit will be used. Homogenate will be transferred to a separate tube and 50 μL PBS used to wash remaining homogenate from the beads. A total of 180 μL of ATL buffer and 20 μL of proteinase K (Qiagen) will be added, and the homogenate vortexed and incubated at 56°C for 4 hours. Following this step, extractions will be performed as previously described
^
16
^.

**
Quantitative polymerase chain reaction
**

Appropriate primers be used for detection of BCG DNA. These are optimised modifications
^
16
^ of an early template complementary to regions flanking the BCG deletion sequence, RD1, and amplify a 196–base pair fragment
^
22
^. Polymerase chain reaction (PCR) analyses will be performed as previously described
^
16

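### The no-blinding statement makes no exception for laboratory readers, which leaves the Phase A agreement comparisons and the Phase B time course open to review bias

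*Protocol article*

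**What the plan says.** The section Blinding and code breaking consists of one sentence: "Participants and researchers will not be blinded within this study". It follows the statement that participants are not randomised, and nothing elsewhere qualifies it.

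The readings at issue are described under Confirmation and quantification of mycobacterial recovery: "Skin biopsy specimens will be cryopreserved and subsequently processed in batch". Homogenate is plated in triplicate, and "Plates will incubated at 37°C for 4 weeks before counting". Stored homogenate later goes to DNA extraction and to quantitative PCR against a standard curve.

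These readings serve three purposes.

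- **Agreement with punch biopsy.** Table 1 lists as a secondary endpoint "Pairwise comparison between culture and PCR quantification by punch and micro skin biopsy", with a parallel endpoint for the skin scrape. Objective 3 and the Phase A description also include the swab. The second study hypothesis expects molecular recovery by minimally invasive biopsy to reach at least 90% of the punch result.
- **Progression to Phase B.** Criteria 3 and 4 both begin "Confirmation of BCG recovery by classical microbiology or molecular techniques". Criterion 3 requires this "from punch biopsy at day 14 in all 10 participants who received intradermal BCG challenge". Criterion 4 requires it from "any of the minimally invasive skin sample technique (swab, scrape and microbiopsy) at day 14 in ≥9 participants".
- **Phase B time course.** Microbiopsies are taken on days 0, 2, 7 and 14 to follow BCG growth.

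The Informed consent section says samples are anonymised, and the data sections assign study numbers. Both hide who the person is. Neither hides the sampling technique, the day or the paired result.

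**The concern.** Phase A has no treatment arms, but it is a comparison of index techniques with a reference standard in the same participants. In such a comparison the masking that matters is that of the person who reads the result. A reader who knows that the punch biopsy grew BCG may be readier to accept one doubtful colony, or a late PCR signal, as positive on the paired microbiopsy. That pushes agreement upward. In Phase B, a reader who knows the day may resolve doubtful plates towards the growth curve that is expected.

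At stake is the choice of sampling technique. A method could be carried into Phase B, and into later studies, on agreement somewhat better than it really has.

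**Working it through.** The document gives no figure for reader error, agreement or power, so there is no stated number to reproduce. The check is a reading of the text, followed by one illustration on assumed values.

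**1. Does the text cover the readers?** The sentence says researchers, without exception. Staff who count plates and call PCR are researchers in the ordinary sense. Their inclusion is an inference, but the natural one. No other section provides for masked reading.

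**2. Where could judgement enter?** Triplicate counts and PCR against a standard curve are fairly objective at high burden. Low burden is foreseeable from the article itself. Under Risk to participant contacts it says that only very low levels of BCG are detectable by swabbing the injection site. The skin swab paragraph reports conflicting literature, including a study that could not culture BCG from swabs. The exposure therefore sits mainly in low-count and near-threshold readings. The 90% hypothesis concerns molecular recovery only, so for that hypothesis it is the PCR call that matters.

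**3. Which endpoints depend on the pairing?** The agreement endpoints and the 90% hypothesis compare each new technique with punch in the same participant, so knowledge of the paired result acts on them directly. The Phase B curve compares days, so knowledge of the day acts on it directly.

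**4. How far are the go criteria affected?** Criterion 4 counts participants with any recovery. Three techniques × two methods = six routes to a positive. With 10 participants, one changed participant moves the observed rate by 1/10, or 10 percentage points. A single doubtful read turns 8/10 into 9/10 only if that participant's other five routes are all negative.

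As an illustration of how sensitive the count is, let p be the true share of participants with recovery, and f the share of truly negative participants who are called positive. Both are assumptions; the documents give neither.

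p′ = p + (1 − p)f

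P(at least 9 of 10) = 10·p′⁹·(1 − p′) + p′¹⁰

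For p = 0.80 and f = 0.25: p′ = 0.80 + 0.20 × 0.25 = 0.85. The probability is 10 × 0.85⁹ × 0.15 + 0.85¹⁰ = 0.347 + 0.197 = 0.544.

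| True recovery p | f = 0 | f = 0.10 | f = 0.25 | f = 0.50 |
|---|---|---|---|---|
| 0.70 | 0.149 | 0.202 | 0.305 | 0.544 |
| 0.80 | 0.376 | 0.439 | 0.544 | 0.736 |
| 0.90 | 0.736 | 0.775 | 0.830 | 0.914 |

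The table shows that a 9-of-10 rule responds to a few calls. It does not estimate f, and it does not show that coding would bring f to zero.

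**5. Is masking practicable?** Biopsy specimens are already frozen and handled in batches, and plates are counted weeks later. Codes can be applied once specimens are processed. The article describes homogenisation for biopsy specimens only, so the point at which swabs and scrapes can be coded would need to be set in the laboratory procedure.

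**The case against.** The strongest reply is that the sentence is generic. In a single-arm study, placed straight after the statement on randomisation, it may mean only that there is no allocation to conceal. The article condenses its laboratory methods and refers to site-specific SOPs, which might already provide coded reading. That is fair, and it is why the inclusion of readers must be called an inference. But the point does not rest on silence. The article makes an unqualified statement, and if an SOP masks the readers, that statement is inaccurate as written and needs the exception.

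A second reply is that knowing the reference requires the punch result to be available first, and the article gives no reading order. This also stands: the exposure is possible, not shown. Batch processing neither guarantees it nor prevents it.

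Third, the read-outs are fairly objective. This holds at high burden and confines the concern to low counts and near-threshold signals.

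A reader might infer more: that one doubtful plate decides whether the study proceeds, and that coding would cure this. The documents do not support either. Criterion 4 accepts culture or molecular recovery from any of three techniques, and it counts detections, not agreement with punch. Every day-14 specimen also comes from a challenged site, so a reader of coded samples would still expect a positive. A confidence interval around 8/10 or 9/10 would not help the stronger reading, because it describes sampling error and not reader bias.

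**Conclusion.** The point holds for the secondary agreement endpoints, the 90% hypothesis and the Phase B time course. As written, the plan allows results to be read with knowledge of technique, paired punch result and study day, and it forgoes an inexpensive safeguard. The likely direction in Phase A is towards better apparent agreement. The size cannot be derived from the document. The probabilities above rest wholly on assumed values and bear only on criterion 4, where the effect of coding is limited, as it is for criterion 3.

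The conclusion assumes that laboratory readers are among the researchers named and that no procedure outside the article masks them. In a single-arm feasibility study with laboratory endpoints, this is a low-priority improvement, not a flaw that undermines the study.

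**What to change.** Amend Blinding and code breaking to say that participants and clinic staff remain unblinded, and that laboratory reading is masked as follows:

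- Plates and DNA extracts carry random codes once specimens are processed.
- Colony counting and PCR calling are done without sight of participant, technique, time point or paired result.
- The positivity cut-off for culture and for PCR is set before any reading.
- Negative controls are included in the batch, so that a reader cannot assume every coded sample comes from a challenged site.
- Codes are broken only after results are locked.

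This reduces the bias but does not remove it, because the staff who take the samples still know the technique and the day. The cost is a coding list and slightly more laboratory administration, including the handling of the negative controls. No extra reader is needed.
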